#### Other Measures

Length of stay, discharge disposition, rehospitalization, institutionalization, and death will be obtained by using an investigator-developed *Weekly Chart Review*. To further help describe usual care we will assess staff knowledge of delirium using our case vignettes[101] at baseline and every 6 months to capture any change in overall level of delirium knowledge per site that might occur due to historical factors or staff turnover in the nursing home. The case vignettes include five standardized cases that depict different hospitalized patients experiencing dementia, hypoactive delirium, hyperactive delirium, hyperactive DSD and hypoactive DSD. The case vignettes were intended to assess staff ability to identify different subtypes of delirium and delirium superimposed on dementia in a standardized format, as well as to gather qualitative data from the staff. All case vignettes were completed by 4 expert panelists. Their overall agreement on the cases was 84%, with a kappa of 0.69. For identification of delirium motoric subtype expert agreement was 100% with a kappa of 1.0[101]. We will also record staffing ratios at each site every six months by accessing the Pennsylvania Department of Health website where these data are published.

We will conduct a three-month follow-up to track the trajectory of delirium resolution. We are not powered to conduct analyses with the data from this three-month follow-up. These data will be used to help calculate the sample size needed for a future multisite study that will focus on long term outcomes of RESERVE-DSD effectiveness. The three month point approximates a Medicare benefit period for skilled care (100 days), so we should be able to capture data reflecting variability on these longer term outcomes as participants will likely be either discharged to home, assisted living or transferred to a long-term care facility for continuing care at that point. We will contact the responsible party by phone and obtain information on the participant's length of stay in post acute care (if we do not have this information at the 30 day point), any additional re-hospitalizations, institutionalization and death. We will interview the responsible party using the CAM and telephone MMSE to assess the participant's current delirium status. In a study of 41 older adults discharged to home following hip surgery, the telephone method of assessing delirium showed a sensitivity of 1.00 and specificity of 0.94[127].

### Statistical Analysis

Prior to conducting any statistical analyses, the distributions of all sample data will be examined. Extreme values will be compared with the original data collection forms in order to identify and correct data entry errors. Following this data validation step, sample distributions will be evaluated to determine if they meet the assumptions necessary for use of normal distribution-based statistical methods. If the data are not normally distributed, suitable transformations will be sought to normalize them. Possible transformations include log, square root, and rank transformations. If the data are not sufficiently normalized by transformation, the analysis may proceed using permutation testing to determine significance levels. Categorical variables will be evaluated using models based on the binomial or multinomial distributions. The design of this study is a two-group randomized design within blocks defined by individual nursing homes. Randomization will be conducted at the participant level, so that intervention groups are crossed with nursing homes, rather than nested within them. Repeated measurements will be made within individual participants for up to 30 days. The statistical methods must appropriately account for within-participant correlation among these repeated measurements.

The primary statistical model will be mixed-model analysis of variance (ANOVA). A term representing individual participants will be included as a random effect in the model in order to account for correlated multiple measurements for each participant. Treatment and covariates will be included as fixed effects. The primary outcome variables are delirium severity and duration, and cognitive and physical functioning.

The primary analyses will be based on intent to treat. Thus, participants will be included in the analyses regardless of their level of participation in the treatments or of their loss to follow-up. Participants who have missing data for some time points will not be excluded from analyses. The methodology incorporates all available measurements for each participant into the analysis. Missing values for some observation times will not cause the participant's entire record to be excluded from the analyses, as may occur in usual repeated measures models.

Potential confounders will be included as covariates in the analysis. If a variable substantially alters either the significance level of a group comparison or a measure of association, that variable will remain in the model in order to control for its confounding effect. Variables that will be evaluated as covariates include those that increase delirium severity and duration, acetylcholinesterase inhibitors, and potential moderators of the association between treatment and outcome.

In order to evaluate differences in change across the study period between the intervention groups, time, and group by time interaction terms will be included in the model. A significant group by time interaction will be of interest, as it would reflect differences in rates of change between the groups. A significant interaction term could yield a non-significant test for the main effect of group, but could reflect an important effect of the intervention. If the test for interaction is significant, the nature of the interaction effect will be evaluated using means plots and post-hoc contrasts.

Hypothesized moderator variables will be evaluated using LISREL and SAS software. Structural models will be specified based on the path diagram presented previously. The path diagram will be used to define the hypothesized structure of the relationships among the variables. Multilevel structural equations modeling (SEM) will be used to evaluate the hypothesized structure, including testing the hypothesized moderator status of the cognitive reserve variables. Tests for moderation are based on regression relationships among the specified variables. These relationships are specified in the SEM model and may be tested based on statistical significance of parameters for direct and indirect effects in the hypothesized model. These relationships can also be tested using sets of mixed-model regression analyses[128-130]. This approach, based on the "Baron and Kenny steps"[128] will be implemented as supplemental analyses using SAS software. Using the regression approach, moderating effects are evaluated as the interaction effect of X and M. Least-squares means with 95% confidence intervals will be used to summarize moderated effects.

One goal of the study is to describe the costs associated with the RESERVE-DSD intervention and developing methods for documenting these costs. This information is important for evaluating the public health impact of the intervention. Because this is a new intervention with little data describing its cost, activity-based costing methods will be used. Determining the cost of the intervention will involve several steps. First, resources used to deliver the intervention will be determined. These resources will include personnel, supplies and other expenses. Next, the amounts used of these resources will be documented. In the case of personnel time, the amount of time spent on activities related to the intervention will be determined using activity diaries for assessment and prescription time, and direct observation by study personnel using the *time on task *measure for the intervention. Finally, the amounts used of each resource will be multiplied by the unit cost of each resource to determine the cost associated with the resource. For personnel costs, the time spent by each provider on activities related to the intervention will be multiplied by the hourly compensation, including benefits, associated with the provider. Finally, costs will be summed across all components of the intervention and divided by the number of patients treated to determine the average cost per patient of delivering the RESERVE-DSD intervention. Because different nursing homes might use different types of personnel for some intervention activities, sensitivity analyses will be used to determine the effect of using different types of personnel on the cost of the intervention. Hence, in addition to the actual average cost of providing the intervention, projected costs based on different types of appropriate personnel providing the intervention will also be constructed. These data will inform a future cost-effectiveness study.

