**Methods/Design:**

This randomized repeated measures clinical trial will involve participants being recruited and enrolled at the time of admission to post acute care. We will randomize 256 subjects to intervention (RESERVE-DSD) or control (usual care). Intervention subjects will receive 30-minute sessions of tailored cognitively stimulating recreational activities for up to 30 days. We hypothesize that subjects who receive RESERVE-DSD will have: decreased severity and duration of delirium; greater gains in attention, orientation, memory, abstract thinking, and executive functioning; and greater gains in physical function compared to subjects with DSD who receive usual care. We will also evaluate potential moderators of intervention efficacy (lifetime of complex mental activities and APOE status). Our secondary aim is to describe the costs associated with RESERVE-DSD.

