## Background

Delirium is a state of confusion characterized by an acute and fluctuating decline in cognitive functioning[1]. The exact cause of delirium is unknown but typically involves a vulnerable patient and a noxious insult such as surgery, infection, or adverse effects from medications[2]. Delirium is common and deadly in older adults with dementia, and is often referred to as delirium superimposed on dementia, or DSD. Over 80% of older adults with dementia experience delirium when hospitalized, and studies report that between 24 and 76% die within one year of the index episode [3,4]. Delirium often persists long past the acute phase of an illness and substantially worsens outcomes in a population already burdened with physical and cognitive deficits [5,6]. Over two thirds of older adults admitted to post acute care exhibit delirium on admission[7]. Unresolved delirium results in an accelerated trajectory of cognitive and physical decline that prolongs hospitalization and rehabilitation, and precipitates premature nursing home placement [4,8-10].

It is difficult to prevent delirium in persons who already have reduced cognitive reserve [11]. Efforts to resolve established delirium are critical to implement because data indicate that when delirium resolves slowly, or never at all, less than 50% of pre-illness functioning is realized[12]. These individuals are at high risk for poor quality of life and institutionalization because of their resultant functional impairments, their care becoming too burdensome for family caregivers to support. Interventions that slow the accelerated downward spiral accompanying DSD have the potential to make a major public health impact by preserving function, preventing premature institutionalization and reducing the $152 billion national burden attributed to delirium [4,13,14].

Unfortunately, interventions that treat DSD are not well-developed because the mechanisms involved in its etiology are not completely understood. Historically, the pathophysiology of delirium has been characterized as a derangement of the functional metabolism of the brain[15]. In support of this theory, studies have found decreased blood flow in varied and diffuse regions of the brain that normalizes once the delirium resolves[16,17]. On a cellular level there is disruption of cholinergic transmission[2,18], dopaminergic excess[19], and elevated markers of inflammation (chemokines and cytokines)[20].

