### Randomization and Control of Cross-Contamination

Randomization will be concealed until after the initial screen and consent are obtained and an ID number is assigned to the participant. The statistician will generate the randomization sequence using a random number generator. Randomization will be conducted in blocks by nursing home site and time to ensure equal assignment across the two groups at the completion of the study and approximately equal assignments throughout the study to control for unknown temporal effects. The statistician will be blinded to treatment coding.

Our team discussed several randomization procedures and we have elected to randomize by participant rather than by site, even though the latter approach is an excellent method for controlling cross-contamination of conditions. There are several reasons for our decision. First, nursing homes are unstable environments[84] and there is evidence indicating that nursing home quality indicators are unstable from one six-month period to the next[85]. Changes in quality indicators may reflect change in quality of care and/or resident profile. Either could potentially impact our outcomes because of their likely effect on usual care. Second, we are confident that we can control treatment contamination within sites, and for the same sample size, randomization by participant will provide greater power than randomization by nursing home.

We control for cross-contamination by conducting all interventions using our trained research assistants (RAs) (not nursing home staff) in an area specifically set aside for these sessions. Nursing homes have provided us with this research space in the past and staff has always respected our procedures for control of cross-contamination. Only the resident scheduled for a particular session will be allowed access to the area for that time period.

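### The one correlation device named for up to 30 daily measurements is a participant random effect; if nothing is added and time is linear, the group-by-time test is likely to exceed its nominal 5% level

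*Protocol article*

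**What the plan says.** The Abstract gives the size of the trial: "We will randomize 256 subjects to intervention (RESERVE-DSD) or control (usual care"). The randomization section aims "to ensure equal assignment across the two groups at the completion of the study", so about 128 per arm.

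The Statistical Analysis section says: "Repeated measurements will be made within individual participants for up to 30 days". It requires that the methods deal properly with correlation within participants, and calls the primary model a mixed-model ANOVA. The random part is described in one sentence: "A term representing individual participants will be included as a random effect in the model in order to account for correlated multiple measurements". The fixed part is: "Treatment and covariates will be included as fixed effects".

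For change over the study period, "time, and group by time interaction terms will be included in the model". The interaction is interpreted thus: "A significant group by time interaction will be of interest, as it would reflect differences in rates of change between the groups". The section adds that the interaction may be significant while the group main effect is not, and that this could still be an important effect of the intervention. A significant interaction is followed by means plots and post-hoc contrasts. The section does not say whether time is a linear term or a factor. It names no random slope, residual correlation structure or robust standard error.

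**The concern.** A single participant term implies that any two days correlate equally, whether one day or 29 days apart. It also implies that, within a group, participants share one rate of change apart from independent daily noise. The article's own account of the condition makes both unlikely. The section on primary outcomes justifies daily measurement by the fluctuating course of delirium, cognition and function. The Background refers to outcomes "when delirium resolves slowly, or never at all", so recovery courses differ between people.

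If participants differ in slope, or neighbouring days are more alike than distant ones, a random-intercept model judges the slope difference against day-to-day noise and leaves out part of its true variance. The standard error is then too small. At stake is a claim of faster recovery in delirium severity, the cognitive scores or the Barthel Index that rests on the interaction alone, which the plan permits.

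**Working it through.** The article gives no effect size, SD, power, alpha or within-person correlation, so there is no stated figure to reproduce. The check compares the variance that a random-intercept fit assigns to a participant's slope with its true variance.

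**Inputs from the article:** 256 participants, equal allocation (128 per arm), daily measurement up to 30 days, one participant random effect.

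**Assumptions:** two-sided alpha 0.05, 30 complete days, linear day, and all slope SDs, residual SDs and autocorrelations below.

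**1. Random slopes, by formula.** Let s be the residual SD and b the SD of individual slopes.
- Sxx for days 1–30 = 30 × (30² − 1)/12 = 2247.5.
- True variance of one participant's slope = b² + s²/Sxx.
- Variance under the random-intercept model = (s² + b²·Sxx/29)/Sxx.
- Type I error = 2·P(Z > 1.96/√ratio), where ratio = true/model.

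For s = 4 points and b = 0.10 points/day:
- True: 0.01 + 16/2247.5 = 0.01712.
- Model: (16 + 0.775)/2247.5 = 0.00746.
- Ratio = 2.29, and 1.96/√2.29 = 1.29, so type I error = 19.6%.

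| Slope SD (points/day) | SD of 29-day change ÷ residual SD | Variance ratio | Type I error |
|---|---|---|---|
| 0.05 | 0.05 × 29/4 = 0.36 | 1.34 | 9.0% |
| 0.10 | 0.73 | 2.29 | 19.6% |
| 0.20 | 1.45 | 5.54 | 40.5% |

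**2. Simulation.** 4000 null trials per row, 128 per arm, 30 complete days, intercept variance 0.5 and residual variance 0.5. The slope rows give the SD of 29-day change in residual-SD units. The last column is a t-test on participants' own slopes, which allows person-specific rates.

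| True correlation | Linear time | Categorical time | Group main effect | Slope-based test |
|---|---|---|---|---|
| Compound symmetry | 0.051 | 0.052 | 0.050 | 0.051 |
| AR(1) 0.2 | 0.109 | 0.062 | 0.054 | 0.052 |
| AR(1) 0.4 | 0.197 | 0.082 | 0.050 | 0.048 |
| AR(1) 0.6 | 0.301 | 0.106 | 0.052 | 0.054 |
| AR(1) 0.8 | 0.462 | 0.151 | 0.052 | 0.053 |
| Slopes 0.25 | 0.066 | 0.051 | 0.051 | 0.045 |
| Slopes 0.50 | 0.118 | 0.050 | 0.056 | 0.046 |
| Slopes 1.00 | 0.290 | 0.063 | 0.048 | 0.051 |

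Under AR(1) of 0.2, 0.4, 0.6 and 0.8, the linear-time model's standard error is 0.83, 0.67, 0.53 and 0.38 of the true one.

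**3. Shorter stays (analytic, linear time).** With 10 days, AR(1) of 0.2–0.8 gives about 10–32%, while the slope scenarios give only 5–6%. With 20 days the ranges are about 10–42% and 5–14%. Serial correlation therefore matters even for short stays; slope variation matters mainly for long ones.

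**4. Power if time is a 30-level factor.** A linear effect with 80% power on 1 df has noncentrality (1.96 + 0.84)² ≈ 7.85. Spread over 29 df, the same noncentrality gives about 25.5% power.

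**The case against.** The strongest reply is that the article says a participant term will be included, not that it is the sole covariance component. It excludes neither random slopes nor a residual structure, and it requires correlation to be handled appropriately. An article commonly leaves such detail to the full protocol or analysis plan, which is not shown. This stands in part: a reader might infer that the model has nothing but a random intercept, and the text does not establish that. But the participant term is given as the means of dealing with the correlation, so a programmer following the text would fit a random intercept.

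Second, the time coding is open. An ANOVA with means plots and post-hoc contrasts suits categorical time at least as well, although rates of change points to slopes. With categorical time most of the inflation goes. This stands. The linear-time inflation and the 29-df power loss are alternatives; they cannot both apply to one fitted model.

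Third, a reader might infer that the error bars are wrong for every primary outcome. The document does not support that. Inflation is nil under compound symmetry. No variance figures are given for any scale, and one residual SD cannot represent the Delirium Rating Scale, Barthel, Digit Span and CLOX alike. Delirium duration is one value per participant and has no group-by-time test, and the group main effect keeps its level in balanced data.

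The permutation option does not answer the concern, because it is triggered by non-normality and not by a wrong covariance.

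**Conclusion.** The concern holds conditionally. The article fixes an interaction about rates of change and names a single correlation device that does not by itself protect that test. If nothing is added and time is linear, the test is likely to exceed 5% for delirium severity, the cognitive scores and the Barthel Index whenever recovery rates vary or adjacent days correlate more than distant ones. With 30 complete days the range runs from about 7% (slopes 0.25) to 41% (slope SD 0.20 with residual SD 4), and from 11% to 46% for AR(1) of 0.2–0.8. These ranges show sensitivity to assumed values; they are not estimates for this trial. The direction is well supported, but the size for any one outcome is unknown.

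**What to change.** For the daily outcomes, state the primary model as a participant random intercept plus a random slope for day and/or a serially correlated residual structure such as AR(1); alternatively, use cluster-robust standard errors by participant. State that day is linear for the primary interaction, and test group-by-time as one pre-specified 1-df difference in slope. In the simulation, a test allowing person-specific slopes held its level in every scenario (0.045–0.054).

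The cost is a sentence or two in the model statement, slightly more modelling work with standard options in the SAS software already planned, and wider confidence intervals for the slope difference. A different summary, such as a mean over treated days, or a limit on day-by-day contrasts, would be a matter of preference and is not needed to resolve this point.

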#### Assessment and Prescription

The selection of activities for each participant will be determined by [name]. Each participant's baseline data, including dementia stage, physical function, and activity interests are reviewed. Based on this assessment, three recreational activities tailored to the participant's functional abilities and designed around themes of their interests will be selected by level of difficulty (easy, moderate, and hard) in each cognitive domain. For example, a participant who has arthritic problems with their hands, a mild stage of dementia, and a history of interest in gardening might be prescribed: identify the sound of a lawn mower (attention); discuss whether the current calendar month is good for planting (orientation); memory tray with three or more garden tools (memory); describe steps to planting a garden (abstract thinking); and having the participant plant flower seeds using adapted hand tools (executive functioning). Using the domain of attention as an example, increasing the level of difficulty might proceed in this fashion: lawn mower sound identification (easy); circle the garden tools in a picture (moderate); item search of vegetables embedded in a "busy" picture (difficult). We provide variety from day to day to encourage cognitive processing and to prevent a practice effect.

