Activity interests will be assessed for participants randomized to RESERVE-DSD by interviewing the responsible party using an adapted version of the *Farrington Leisure History Checklist*[88]. This checklist contains 150 recreational activities categorized by games, social, outdoor and cultural activities. These data will be used to adapt cognitively stimulating recreational activities around themes that match participants' interests.

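### The stated primary model names neither the nursing home that blocks randomisation nor the pre-treatment outcome score, which costs precision on the group main effect

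*Protocol article*

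**What the plan says.** The section on randomisation states: "Randomization will be conducted in blocks by nursing home site and time". Statistical Analysis repeats this: "The design of this study is a two-group randomized design within blocks defined by individual nursing homes". It adds that arms are crossed with homes.

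The same section then gives the primary model. Participant is a random effect, and for the rest "Treatment and covariates will be included as fixed effects". Time and group by time are added to assess differences in change.

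Candidate covariates appear in two places:
- **Methods/Design, after the trial flow figure:** dementia stage, comorbidity, age, CNS-active drugs, pain, infection, dehydration, APOE status and lifetime mental activity.
- **Statistical Analysis:** factors that worsen delirium, acetylcholinesterase inhibitors and the potential moderators.

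Neither list contains the nursing home or the starting value of the outcome. A covariate stays in the model if it substantially alters the significance level of a group comparison or a measure of association.

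Delirium severity, cognition and physical function are assessed every morning by blinded assistants, and sessions take place in the afternoon. Delirium duration is a single count of days per participant.

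**The concern.** A factor that restricts randomisation belongs in the analysis. Blocking removes differences between homes from the sampling error of the treatment contrast. If the model has no term for home, those differences stay in its estimate of residual variation, and the standard error no longer matches the design. The article expects homes to matter: the five sites were chosen as a deliberate mix, and it plans to monitor differences between them.

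The pre-treatment score is usually the strongest single predictor of later scores on the same scale. If it is not in the model, stable differences between participants remain in the comparison of group means.

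The retention rule does not fill the gap. A blocking factor is balanced by design, so it may barely move the estimate. Selecting terms by their effect on the significance level is no substitute for naming them in advance. At stake is precision for the group main effect on the repeated outcomes and for delirium duration.

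**Working it through.** **Inputs from the protocol article.** The Abstract gives the total: "We will randomize 256 subjects to intervention (RESERVE-DSD) or control (usual care"). Assignment is to be equal between arms, so 128 per arm, in five homes (Setting and Participants). The article states no alpha, power, effect size, standard deviation, site ICC or baseline correlation, so 256 cannot be reproduced.

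**Assumptions.** Two-sided alpha 0.05; one summary value per participant with total SD 1; site ICC 0.05 to 0.10; correlation r between the baseline score and the follow-up mean of 0.5 to 0.7.

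**Step 1: site and the standard error.** With arms balanced within homes, the true standard error of the group difference is √(2/128) × √(1 − ICC). A model without site reports √(2/128). The ratio is 1/√(1 − ICC):
- ICC 0.05: 1/√0.95 = 1.026, so 2.6% too large.
- ICC 0.10: 1/√0.90 = 1.054, so 5.4% too large.

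**Step 2: type I error with site omitted.** This is 2 × P(Z > 1.96 × ratio):
- ICC 0.05: 2 × P(Z > 2.011) = 0.044.
- ICC 0.10: 2 × P(Z > 2.066) = 0.039.

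A simulation (five homes, assumed permuted blocks of four, 8,000 runs per setting) gave 0.045 and 0.041 without site, and 0.049 and 0.050 with it.

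**Step 3: power lost through site.** With 128 per arm, the standardised difference detectable at 80% power without adjustment is (1.96 + 0.842) × √(2/128) = 0.35. At that difference:

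| ICC | Site omitted | Site included |
|---|---|---|
| 0.05 | 80.6% | 82.0% |
| 0.10 | 81.3% | 84.0% |

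**Step 4: baseline score.** Adjustment multiplies the variance of the group main effect by 1 − r². Power below is for the same difference with ICC 0:

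| r | Variance factor | Reduction | Equivalent unadjusted total | Power |
|---|---|---|---|---|
| 0.5 | 0.75 | 25% | 256/0.75 = 341 | 89.9% |
| 0.7 | 0.51 | 49% | 256/0.51 = 502 | 97.5% |

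**Step 5: where this applies.** A constant shift for a home, or a stable difference between participants, adds the same amount to all of a participant's scores and leaves that participant's slope unchanged. The group-by-time test is therefore essentially unaffected, unless homes also differ in time trend. Steps 1 to 3 apply to the group main effect and to delirium duration. Step 4 applies to the group main effect on the repeated outcomes. Duration has no baseline value of its own; baseline severity could serve as a covariate, but the range used for r cannot be carried over to it.

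**The case against.** The strongest reply is that this is a condensed article whose covariate lists are open-ended, so an unseen analysis plan may add both terms. Nothing in the text excludes them, and the first morning score may already enter as a repeated response. This stands in part: the terms are not named, which is less than saying they are ruled out. But the article does set out its model terms and covariates directly after describing the blocks, and its one rule for adding covariates is the wrong rule for these two.

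Three stronger readings are tempting but not supported:

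- **False positives.** A reader might infer that a mismatched standard error inflates type I error. It does the reverse: the test is conservative, and only slightly so at modest ICC.
- **Wasted power throughout.** A reader might take 341 to 502 as the trial's effective shortfall. Those totals rest on an assumed correlation and concern only the group main effect. The article assesses differences in change through group by time, where little would be gained.
- **Biased baselines.** Allocation may be released after screening, consent and ID assignment, and one interview is arm-specific: "Activity interests will be assessed for participants randomized to RESERVE-DSD by interviewing the responsible party". A reader might infer that baseline scores are collected with the arm known. However, blinded assistants collect the outcome scores, and the interest checklist only tailors activities; it is neither an outcome nor a listed covariate. The randomisation section gives the earliest point of release and does not say that baseline collection follows it. The item most plausibly open to influence is the LEQ informant interview.

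**Conclusion.** The point holds as a matter of efficiency and prespecification. The stated model does not carry the blocking factor or the pre-treatment score, and the covariate rule could leave either out. The site omission is small and errs on the safe side, costing about 1.4 to 2.7 percentage points of power at the assumed ICCs. Most of the available gain comes from the baseline score. All sizes depend on an ICC and a correlation that the article does not give. The documents do not support a claim of inflated type I error, of lost power for the group-by-time test, or of baseline scores biased by known allocation.

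**What to change.** 1. Name nursing home as a fixed effect in every primary model, including that for delirium duration.
2. Name the first pre-session score for the DRS, the Barthel Index and each cognitive test, either as a covariate (with the outcome series starting afterwards) or as a baseline response constrained to a common mean in both arms. For duration, use baseline DRS as the covariate.
3. Exempt both terms from the covariate retention rule.
4. State how participants without a pre-session score are handled. Sessions are to begin within 24 hours of admission and in the afternoon, while assessments are in the morning, so a first session could precede any assessment. Controls have no session, so the rule should be written in terms of enrolment time and apply identically to both arms.
5. Where feasible, complete the LEQ informant interview before the arm is revealed. Holding allocation until every baseline measure is done could conflict with the 24-hour start, so those passages would have to be reconciled before any such requirement is added.

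The cost is 4 degrees of freedom for site, one for each baseline covariate, and minor analysis work. The scores come from the assessments already planned, except where the first assessment falls after the first session.
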